| Objectives | The main objective is to evaluate the effectiveness of POTs in preventing fall injuries during physical activities in the military context.  Secondary objectives:  The first secondary objective is to test the mechanistic hypothesis that POTs can reduce the risk of fall injury by improving postural awareness.  The second secondary objective is to test the mechanistic hypothesis that POTs can reduce the risk of fall injury by decreasing the intensity of the psychobiological stress response during physical activities in the military context.  The third secondary objective is to use machine learning to develop a predictive model of the risk of fall injury, based on clinical (the BESS test) and paraclinical (posturography) measurements taken prior to the start of physical activities in the military context.  The fourth secondary objective is to evaluate the persistence over time of the effectiveness of a POT intervention in preventing the risk of fall-related injury. The rate of fall injuries will be compared for POTs and active control groups among participants who continue to engage in physical activities after the end-of-study visit (and complete the selection course). |
| Research outline | This is an open, prospective, controlled, single-center cohort study. |

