Against this background, the POSITION project aims to study the cognitive mechanisms involved in body awareness, both as a risk factor in fall injury, and as a target for a prevention strategy that aims to reduce the injury rate by improving postural control.

This research project was prompted by epidemiological observations carried out during the French Marine Commando Selection Course (STAC). Medical unfitness due to incapacity is the leading cause of failure (70%). Acute trauma is the principal pathology (60%), typically involving the lower limbs (Bertrand, 2016; Longin, 2015; Morinière, 2013). A review of the circumstances surrounding the trauma highlighted that a fall due to a loss of balance was the cause in 90% of cases (Bertrand, 2016). These data suggest that postural balance could play a role in the injuries encountered during the STAC. The activities that candidates must undertake require them to have extremely good postural balance: trainees carry heavy loads (a combat bag and a weapon, weighing 15 kg) for prolonged periods, and complete extreme challenges that are run at-height in all weather conditions. Epidemiological data collected during the course show that the leading activity resulting in trauma is the ‘jungle’ challenge, which involves overcoming obstacles up to 5 meters high with no safety net (Morinière, 2013). Moreover, preliminary (unpublished) epidemiological data collected from other military units (the National Gendarmerie, the 1st Marine Infantry Parachute Regiment, the 13th Parachute Dragoon Regiment, the 10th Air Parachute Commando, and the Fusiliers Marins [Navy Riflemen] School, Paris Fire Brigade) seem to confirm the high rate of trauma linked to a loss of postural balance during physical activities.

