## Secondary objectives

The study has 4 secondary objectives:

1. The first is to test the mechanistic hypothesis that POTs reduce the risk of fall-related injury by improving postural awareness.
2. The second is to test the mechanistic hypothesis that POTs reduce the risk of fall injury by decreasing the intensity of the psychobiological stress response during physical activities in the military context.
3. The third is to use machine learning techniques to develop a predictive model of the risk of fall injury, based on a clinical test (BESS) and paraclinical (posturography) measurements taken before physical activities begin.
4. The fourth is to evaluate the persistence over time of the effectiveness of a POT intervention in reducing the risk of fall injury. The assessment will be based on participants who continue to engage in physical activities after the end-of-study visit (and who complete the selection course); the analysis will compare the rate of fall injuries for POTs and active control groups.

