## Secondary endpoints

Criteria for meeting the study’s four secondary objectives are as follows:

- - 1. The first secondary objective comprises two evaluation criteria: 1) self-reported scores on the Postural Awareness Scale (APPENDIX 3) pre- and post-intervention, and at the start of each session; 2) variation in measures of postural balance pre- and post-intervention.
    2. The second objective also comprises two criteria: 1) self-reported scores on Cohen’s Perceived Stress questionnaire (APPENDIX 3) pre- and post-intervention, and at the start of each session; 2) variation in measures of allostatic load in saliva pre- and post-intervention (the corticotropic axis: cortisol, DHEA, oxidative stress; the autonomic nervous system: alpha amylase and chromogranin A).
    3. The evaluation criterion for the third secondary objective will be the correct prediction of the risk of fall injury by the machine learning model.
    4. The evaluation criterion for the fourth secondary objective will be the rate of fall injuries in each of the two groups (POTs *vs.* active control), in the period between the end of the study and the end of the selection course. Information about when each participant left the course will be collected from the physician responsible.

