**Analysis of secondary objectives**

For the first secondary objective, the effect of the POTs intervention on postural awareness will be evaluated by comparing the following for the POTs group: (*i*) scores on the Postural Awareness Scale at the six measurement times (repeated measures ANOVA), and (*ii*) posturography measurements pre- and post-intervention (paired samples comparison of means).

For the second secondary objective, the effect of the POTs intervention on the psychobiological stress response will be evaluated by comparing the following measures for the POTs group at all six measurement times: (*i*) scores on Cohen’s Perceived Stress Questionnaire (repeated measures ANOVA), and (*ii*) biological stress variables (paired samples comparison of means).

For the third secondary objective, machine learning will be used to evaluate the accuracy of the predictive model of the risk of fall injury using the following calculation:

|  | $\text{Accuracy=}\frac{\text{True }\text{Fall-related injury }\text{participants + True }\text{Non-fall }\text{participants}}{\text{Total number of participants}}$ |  |
| --- | --- | --- |

where N_prediction of trauma_ is the number of participants for whom the machine learning model predicts the occurrence of a fall injury and who do, in fact, suffer a fall injury during the selection course; N_prediction of_ _good health_ is the number of participants for whom the model predicts the non-occurrence of a fall injury and who do not, in fact, suffer a fall injury during the selection course; and N_total_ is the total number of participants included in the study.

For the fourth secondary objective, the long-term effectiveness of the POTs intervention in preventing fall injuries between the end of the study and the end of the selection course will be evaluated using a comparative survival analysis (the Cox model). Survival curves for POTs and active control groups will be compared using the log-rank test.

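### The persistence objective counts only participants who complete the selection course, a condition settled during the outcome window and absent from the endpoint and analysis sections

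*Protocol*

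**What the plan says.** The population for objective 4 is stated twice. Under Objectives, Secondary objectives: "The assessment will be based on participants who continue to engage in physical activities after the end-of-study visit (and who complete the selection course"). The Research Summary makes the comparison "among participants who continue to engage in physical activities after the end-of-study visit (and complete the selection course").

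The endpoint and analysis sections carry no such condition. Under Secondary endpoints, the outcome is the rate of fall injuries in each group "in the period between the end of the study and the end of the selection course", followed by: "Information about when each participant left the course will be collected from the physician responsible". Under Analysis of secondary objectives, effectiveness "between the end of the study and the end of the selection course will be evaluated using a comparative survival analysis (the Cox model"), with a log-rank comparison of the survival curves. The corresponding rows of the Research Summary (evaluation criteria and statistical analysis) also leave the condition out.

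On why candidates fail a course, the background section reports data from the marine commando selection course (STAC). Medical unfitness is the leading cause of failure, at 70%. It continues: "Acute trauma is the principal pathology (60%), typically involving the lower limbs". A fall after loss of balance is given as the cause in 90% of cases.

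**The concern.** Whether someone completes the course is settled after the risk period for this objective begins, and in the same window in which the outcome is counted. A fall injury can end a candidate's course. A participant who is injured late and leaves is then excluded because of the event the analysis is meant to count, while an uninjured participant who finishes is kept. A survival analysis should define its risk set by what is known when follow-up starts, not by what happens later.

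At stake are the late injury rates in both groups, the number of events available, and possibly the direction of the comparison. The protocol also gives two incompatible accounts of the analysis set. If everyone analysed has finished, leaving dates have little use for this objective. If leaving dates are used for censoring, the analysis set is not restricted to completers.

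**Working it through.** **No figure to reproduce.** The protocol gives no expected rate, event count or sample size for objective 4. Its 200 per group is sized on the primary endpoint and is not touched by this point.

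**How far injury explains non-completion.** The inputs are the STAC percentages. If they are nested, acute trauma accounts for 0.70 × 0.60 = 42% of failures, and loss-of-balance falls for 0.70 × 0.60 × 0.90 = 38%. That leaves 30% non-medical failures and 70% − 42% = 28% other medical failures. Acute trauma is then the largest identified cause, but not a majority. These are shares of failures. They do not give the probability that an injured participant leaves.

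**What the restriction does to the rates.** Let p be the late fall-injury risk, q the probability of leaving after such an injury, and r the probability of leaving otherwise. Then

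rate among completers = p(1 − q) / [p(1 − q) + (1 − p)(1 − r)].

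All values of p, q and r below are assumptions. Take p = 0.30 for control and 0.20 for POTs. With q = 0.70 and r = 0:

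- Control: 0.09 / (0.09 + 0.70) = 11.4%.
- POTs: 0.06 / (0.06 + 0.80) = 7.0%.

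For every 100 participants at risk in each group, 30 and 20 injuries occur, and 9 and 6 remain in the analysis. The fraction of events lost equals q.

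**What it does to the contrast.** With r equal in the two groups, the odds ratio among completers is the true odds ratio × (1 − q for POTs) / (1 − q for control). The true odds ratio is (0.20/0.80) / (0.30/0.70) = 0.583.

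| q, control / POTs | r | Control | POTs | Risk ratio | Odds ratio |
|---|---|---|---|---|---|
| No restriction | – | 30.0% | 20.0% | 0.67 | 0.583 |
| 0.70 / 0.70 | 0 | 11.4% | 7.0% | 0.61 | 0.583 |
| 0.90 / 0.90 | 0 | 4.1% | 2.4% | 0.59 | 0.583 |
| 0.50 / 0.50 | 0.10 | 19.2% | 12.2% | 0.63 | 0.583 |
| 0.70 / 0.70 | 0.10 | 12.5% | 7.7% | 0.62 | 0.583 |
| 0.90 / 0.70 | 0.10 | 4.5% | 7.7% | 1.69 | 1.75 |
| 0.70 / 0.90 | 0.10 | 12.5% | 2.7% | 0.22 | 0.19 |

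If every injured participant leaves (q = 1), completers have no events and no comparison is possible.

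With equal q, the absolute rates and the event count fall while the relative effect is roughly kept. With unequal q, the estimate can move either way and can change sign. Unequal q is possible here because the study is open (Type of experiment) and the two groups run in successive years (Study outline, Randomization), so injury severity or decisions about returning to the course could differ between them. The protocol does not show that they do.

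**The case against.** The strongest reply is that the sections which would govern the analysis never apply the restriction. The endpoint and the Cox and log-rank analyses are defined without it, and leaving dates are collected. The words about completing the course may only loosely describe people who carry on after the end-of-study visit. This is plausible, and it makes the point partly one of reconciliation. It does not remove it: the restricted wording is the only description of the analysis population for objective 4, it appears twice, and nothing withdraws it.

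A second reply is that the planned measure is relative, and with equal leaving after injury the odds ratio does not change. That stands for the equal case only.

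A reader might also infer three stronger things that the documents do not support:

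- **That the relative contrast is pulled towards no effect.** Under equal leaving, only the absolute difference shrinks. In the example the risk ratio moves from 0.67 to 0.61, slightly away from 1.
- **That most late injuries are certain to be lost.** The 70% in the background section is a share of failures, not the share of injured participants who leave. It also comes from STAC, not from the six study units.
- **That removal of more injury-prone controls in the first three weeks is part of this error.** Selection before the end-of-study visit affects any late-period comparison, and dropping the completion condition does not cure it. It also cannot be sized from the 50% and 35% in the sample-size section, which carry no time window.

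**Conclusion.** The point holds as a defect in the definition of the objective 4 population. As worded, inclusion is conditional on a later event that the outcome can prevent, and the wording conflicts with the endpoint and analysis sections.

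The consequence that follows directly is understated late injury rates and lost precision, to the extent that injured participants leave. Under the assumed 30% and 20% risks with 70% of the injured leaving, the rates become 11.4% and 7.0%. The true extent is unknown, because the protocol gives no leaving probability. Bias in the relative effect is conditional: it needs leaving after injury to differ between the groups, which the design permits but the documents do not establish.

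This concerns one secondary objective. The primary analysis is unaffected.

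**What to change.** In both the Research Summary and the Secondary objectives, delete the parenthetical requiring completion of the course. Define the risk set as all participants still on the course at the end-of-study visit. Follow each to the first later fall injury, censoring at the recorded leaving date or the end of the course, whichever comes first. State that an injury which leads to leaving counts as an event on its own date, so that it is not lost to censoring on the same day. Repeat this definition in the analysis section so that the four places agree.

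Add a sentence acknowledging that those still on the course at the end-of-study visit are already a selected group, possibly selected differently in the two years, and that persistence must be interpreted with this in mind.

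The cost is a wording amendment. The endpoint already requires late injuries to be recorded, and leaving dates are already to be collected.

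### Objective 4 limits the persistence analysis to course completers, a status that a late fall injury can prevent, while the endpoint and analysis sections carry no such limit

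*Protocol*

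**What the plan says.** The population for objective 4 is stated twice. The Secondary objectives section says: "The assessment will be based on participants who continue to engage in physical activities after the end-of-study visit (and who complete the selection course". The objectives row of the Research summary makes the comparison "among participants who continue to engage in physical activities after the end-of-study visit (and complete the selection course". In both places completion is a second condition, added to still being active after the end-of-study visit.

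The Secondary endpoints section sets the window as "in the period between the end of the study and the end of the selection course", gives the rate for each of the two groups, and names no completer subset. It adds: "Information about when each participant left the course will be collected from the physician responsible".

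The analysis of secondary objectives says that long-term effectiveness "between the end of the study and the end of the selection course will be evaluated using a comparative survival analysis (the Cox model", with a log-rank test, again without a restriction. The evaluation-criteria and statistical-analysis rows of the Research summary have none either.

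**The concern.** A participant enters the analysis set only by finishing the course, which is settled at the end of the outcome window, and the outcome can prevent it. Someone whose late fall injury forces them off the course is not a completer, so both the person and the event disappear. The Cox model and log-rank test would then describe only fall injuries that a participant could finish the course with.

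Two things are at stake. The first is information: events are lost in both arms, from an analysis that starts with fewer people than the primary one. The second is bias: if the chance that an injury ends the course differs between arms, the filter removes different shares of the events and the comparison no longer reflects late injury risk.

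The leaving date points to a different intention. Its natural use is to end follow-up for people who leave, and it has little use if leavers are excluded.

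**Working it through.** **The plan's own figures.** The protocol states no size or power for objective 4. The 200 per group is for the primary endpoint: 50% v 35%, two-sided 5%, power 0.80 gives 170 per group, or 183 with continuity correction. Divided by 0.9 for drop-out these are 189 and 204, so 200 fits the corrected formula. It says nothing about the late period.

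**Inputs.**
- From the protocol: 200 per group and fall-injury rates of 50% and 35%. Uninjured at the end of the intervention: 200 × 0.50 = 100 control and 200 × 0.65 = 130 POTs, ignoring drop-out and other departures.
- Assumed: late fall-injury risk r of 30% (control) and 15% (POTs).
- Assumed: q, the share of late fall injuries that end the course, taken from 0.3 to 0.9.

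**Formulas.**
- Completers: n(1 − rq).
- Events among completers: nr(1 − q).
- Rate among completers: r(1 − q) / [r(1 − q) + 1 − r].
- Power: two-proportion test, two-sided 5%, pooled variance under the null.

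**Same q in both arms.**

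| q | Completers, control v POTs | Rate, control v POTs | Total events | Power |
| --- | --- | --- | --- | --- |
| 0 (everyone at risk) | 100 v 130 | 30.0% v 15.0% | 49.5 | 0.78 |
| 0.3 | 91.0 v 124.2 | 23.1% v 11.0% | 34.7 | 0.66 |
| 0.5 | 85.0 v 120.3 | 17.6% v 8.1% | 24.8 | 0.54 |
| 0.7 | 79.0 v 116.4 | 11.4% v 5.0% | 14.9 | 0.38 |
| 0.9 | 73.0 v 112.5 | 4.1% v 1.7% | 5.0 | 0.18 |

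The share of events lost is exactly q. The filter multiplies the injury odds in each arm by (1 − q), so with equal q the odds ratio stays at (0.15/0.85)/(0.30/0.70) = 0.41 in every row. The hazard ratio is only roughly preserved: in a simulation with 20,000 per arm and late risks of 50% v 35%, it moves from about 0.62 in everyone to 0.58 in completers at q = 0.7.

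**Different q by arm, no true effect.** Take r = 30% in both arms, with q = 0.7 in control and 0.5 in POTs.
- Control: 0.30 × 0.3 = 0.09, and 0.09/(0.09 + 0.70) = 11.4%.
- POTs: 0.30 × 0.5 = 0.15, and 0.15/(0.15 + 0.70) = 17.6%.

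Equal risk appears as harm from POTs, with an odds ratio of 0.5/0.3 = 1.67.

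**When a true benefit would reverse.** The POTs odds among completers must exceed the control odds, so 1 − q(POTs) must exceed k × [1 − q(control)], where k is the ratio of true late odds, control to POTs. For 30% v 15%, k = 2.43:
- q(control) = 0.7: q(POTs) must be below 1 − 2.43 × 0.3 = 0.27.
- q(control) = 0.5: 1 − 2.43 × 0.5 is negative, so reversal is impossible.
- q = 0.7 v 0.5: the rates are 11.4% v 8.1%, so POTs still looks better.

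With other assumed late risks the threshold at q(control) = 0.7 is easier to meet: below 0.44 for 50% v 35%, and below 0.54 for 20% v 14%.

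**The case against.** The best defence is that the sections which govern the analysis are sound. The endpoint definition and the Cox and log-rank specification cover the whole window with no completer limit, and the leaving date is collected for each participant. On that reading the parenthesis is loose wording in the objective and leavers were always meant to be analysed. This largely stands as to intention, and it makes the point a conflict to reconcile. It does not remove the point: the condition appears in both statements of the objective, and an analyst who follows them would discard outcome events.

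A reader might infer that the filter reverses a true benefit of POTs. The documents do not support that. Reversal requires injured POTs participants to leave clearly less often than injured controls. The protocol hypothesises fewer fall injuries, not milder ones, and gives no exit probability for either arm. The false-harm example above starts from equal true risk, so it is a null made to look like harm, and a difference of that size would be declared significant only about 21% of the time.

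A reader might also take q from the scientific justification, which attributes 70% of course failures to medical unfitness and reports that "a fall due to a loss of balance was the cause in 90% of cases". Those figures come from the marine commando course, which is not among the six listed units. The 70% is a share of course failures, not the share of fall injuries that end a course. They make exit after injury plausible but do not measure q, so a claim that most events are lost holds only if q exceeds 0.5.

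Finally, the filter is not confined to the injured: it also drops people who leave for other reasons and keeps injured people who finish.

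**Conclusion.** The point holds as a conflict within the protocol, with a real cost if the objective is followed as written. Both statements of objective 4 condition on a status that the outcome can prevent; the endpoint and analysis sections do not.

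The certain consequence, for any q above zero, is loss of events in proportion to q. Under the assumed 100 v 130 at risk and 30% v 15% late risk, power drops from 0.78 to between 0.66 and 0.18 as q runs from 0.3 to 0.9. With equal q, direction and odds ratio survive. Bias, including a possible false harm, needs q to differ by arm. That is possible, because the arms run in successive years, open and without randomisation, but nothing in the protocol shows that it will happen. Late risk and q are assumptions throughout.

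This is the fourth of four secondary objectives, and the primary endpoint and sample size are unaffected. It should be fixed before analysis, but it is not critical to the trial.

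**What to change.** 1. Delete the completer condition from objective 4 in the Secondary objectives section and in the Research summary, so that both agree with the endpoint and analysis sections.
2. Define the population as every participant still on the course and free of a fall injury at the end-of-study visit. If participants injured earlier who remain on the course are to be included, say so and count only new injuries. The calculation above excludes them, so the choice has to be written down.
3. Count the first late fall injury as an event at its date, including when it ends the course.
4. Censor everyone else at the recorded leaving date or at the end of the course.

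The cost is one phrase removed in two places and two or three sentences added. The leaving date is already planned; the date of each late fall injury must be recorded as well, which the survival analysis needs in any case. The change should be made before any outcome data are examined, so that the population is not chosen after the results are seen.
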